### Participant timeline

Participants will be followed for 28 days. At the final visit of the last participant, clinical status data of all individuals, regardless of trial completion or withdrawal, will be obtained. The details of the timeline are presented in Table 1.

**TABLE 1 T1:** Schedule of enrolment, interventions, and assessments.

Timepoint	Study period					
	Enrolment	Allocation	Intervention	Days 3, 5, 7	CRRT period	Day 28/discharge
Timepoint	-t1	0	t1	t2∼t5		t6
Enrollment: Eligibility assessment Informed consent Allocation Etiology, baseline radiological severity (CTSI/EPIC score), IAH grade, surgical/interventional procedures						
	X					
	X					
					
	X					
Interventions: Nafamostat mesylate Heparin						
		X			X	
		X			X	
Assessments: CRRT circuit/filter lifespan SOFA and APACHE II scores§ Inflammatory biomarkers* Pancreatic enzymes (amylase, lipase)* Coagulation parameters† Time to successful enteral nutrition Blood transfusion requirements ICU and hospital length of stay Clinical outcomes‡ Adverse event monitoring End-of-study assessment						
			X	X	X	
		X		X		
		X		X		
		X		X		
		X		X		
				X		
				X		
						X
						X
			X	X	X	X
						X

*Inflammatory biomarkers and pancreatic enzymes include PCT, CRP, IL-6, IL-8, IL-10, and TNF-α, amylase, and lipase, assessed at baseline (Allocation, Day 1) and on days 3, 5, and 7 after enrollment. †Coagulation parameters include aPTT, PT, fibrinogen, and platelet count, assessed at baseline (Allocation, Day 1) and on days 3, 5, and 7 after enrollment. ‡Clinical outcomes include blood purification dependency, duration of mechanical ventilation, and all-cause mortality at 28 days. §SOFA and APACHE II scores are assessed at baseline (Allocation, Day 1) and on days 3, 5, and 7 after enrollment.

### Sample size estimation

The sample size was estimated based on the primary endpoint, which was average service life of the CRRT circuit lifespan or filter (hours). The assumed baseline value of approximately 30 h for the heparin group, together with the standard deviation used in this calculation, were derived from the pooled filter-lifespan data summarized in the network meta-analysis of CRRT anticoagulation strategies by Zhou et al. and the review of circuit-survival determinants by Tsujimoto and Fujii, which indicate that heparin-anticoagulated circuits typically survive on the order of 20–40 h with considerable between-study variability (17, 32). Because the standard deviation of filter lifespan varies significantly across studies, we deliberately chose a relatively conservative value (σ = 8 h) toward the higher end of the reported range, to avoid underestimating the required sample size. A minimum clinically important difference of 4 h (an approximately 13% relative extension over the assumed heparin baseline) was prespecified not purely on statistical grounds but because a gain of this magnitude would be expected to translate into approximately one fewer circuit change per patient over a typical treatment course, with corresponding reductions in nursing workload and blood loss associated with circuit priming and disconnection, as well as lower filter and consumable costs—benefits that are clinically and economically meaningful even though the absolute increase in hours is modest. Assuming a two-sided α level of 0.05 and a power (1–β) of 80%, the sample size was estimated using the approximate formula for comparing the means of two independent samples, resulting in a sample size of approximately 63 cases in each group. Taking into account the approximately 10% dropout rate, it is necessary to recruit 70 participants in each group.

### Recruitment

The recruitment of participants was conducted in the intensive care unit of Weifang People’s Hospital. This intensive care unit has 110 beds. The researchers will conduct a comprehensive assessment of admitted patients. If the patients meet the inclusion criteria, the researchers will fully explain the study to the patients or their legal representatives and answer all their questions, ultimately assisting in completing the informed consent procedure.

### Assignment of interventions: allocation

#### Sequence generation

A statistician who was not involved in the trial used the SPSS 24.0 software to generate a random allocation sequence. Based on the random allocation results, the participants were randomly assigned to the nafamostat mesylate group or the heparin group in a 1:1 ratio.

#### Allocation concealment mechanism

The randomized code and allocation results will be encapsulated in an opaque envelope and handed over to designated personnel for proper custody. To ensure the fairness of the evaluation of the trial results, the randomized results will not be known to the personnel involved in data collection and statistics.

#### Implementation

After obtaining the informed consent of the participants, the trained researchers will open the corresponding envelopes. Participants were randomly assigned to the corresponding groups based on the results in the envelopes (the nafamostat mesylate group or the heparin group).

### Assignment of interventions: blinding

#### Who will be blinded

Due to the differences in management methods and monitoring requirements for various intervention measures, it is not feasible to implement blinding for clinical physicians and nurses. Therefore, this trial will be an open-label trial, but the result evaluators and statisticians will not know the specific treatment allocation.

#### Procedure for unblinding if needed

Not applicable. No blinding was implemented for participants or clinicians. Outcome assessors and statisticians were blinded to group allocation. Therefore, no unblinding procedure was required.

### Data collection and management

#### Plans for assessment and collection of outcomes

We collect data using case report forms. When patients are enrolled in the study, researchers will collect relevant demographic data [such as gender, age, and body mass index (BMI)] from the hospital’s medical records, major comorbidities (such as hypertension, diabetes, coronary artery disease, etc.), the causes of pancreatitis, and use the SOFA and APACHE II scores to assess the severity of the patients’ conditions. To further characterize baseline disease severity, the etiology of pancreatitis (biliary, alcoholic, hypertriglyceridemia-related, post-ERCP, or other), hemodynamic status at enrollment (mean arterial pressure, vasopressor requirement and dose, and serum lactate), radiological severity on the earliest available abdominal CT scan scored using the CT Severity Index (CTSI) and the Extrapancreatic Inflammation on CT (EPIC) score (23), which quantifies pleural effusion, ascites, and retroperitoneal or mesenteric fluid collections, the presence and grade of intra-abdominal hypertension (IAH, defined by bladder pressure measurement according to World Society of the Abdominal Compartment Syndrome criteria), and any surgical or interventional procedures performed (e.g., percutaneous catheter drainage, minimally invasive or open necrosectomy, decompressive laparotomy) will also be recorded at baseline.

Furthermore, the researchers will collect the necessary data based on the results of the laboratory tests, and record the therapeutic measures taken, the disease progression, as well as all adverse events (AE) observed. Laboratory data will comprise blood culture results, white blood cell count, liver and renal function parameters, and coagulation profiles. Disease progression will be assessed using baseline severity scores and serum biomarkers, including the Sequential Organ Failure Assessment (SOFA) score, the Acute Physiology and Chronic Health Evaluation II (APACHE II) score, serum pancreatic enzymes (amylase and lipase), procalcitonin (PCT), C-reactive protein (CRP), interleukin-6 (IL-6), interleukin-8 (IL-8), interleukin-10 (IL-10), and tumor necrosis factor-α (TNF-α). On days 1, 3, 5, and 7 after randomization, follow-up data will be collected, and changes from baseline will be derived to examine longitudinal trends.

#### Plans to promote participant retention and complete follow-up

This study will be conducted in the ICU, and most outcomes will be assessed during hospitalization. Therefore, the risk of loss to follow-up is expected to be very low. Monitoring during CRRT and standard clinical and laboratory assessments are part of routine intensive care unit care. If the patient is transferred to general ward before all planned observations are completed, the required result data will be obtained from the electronic medical record. If the patient has been discharged, the researchers will contact the participant or their family by phone. Reasons for withdrawal or incomplete follow-up will be recorded.

#### Data management

We have established an independent data management team. The members of this team were unaware of the treatment allocation. They were responsible for regular data audits and source data verification. In addition, this independent data management team was also responsible for the statistical analysis of the final data. To protect patient privacy, the personal identification information of the patients was removed and replaced with the study number before analysis. The data management team will conduct strict supervision over the data. The ethics committee has the right to terminate this research under reasonable circumstances.

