### Strategies to improve adherence to interventions

This intervention will be implemented by trained research staff during the continuous renal replacement therapy (CRRT) process of the patients. The patients are unaware of the intervention measures they are receiving and will not be involved in the medication administration process. The researchers will monitor the patients’ compliance through bedside checklists and daily review of treatment records. Any deviations from the trial protocol will be recorded along with the reasons.

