#### Confidentiality

The personal information of all participants will be replaced by unique identification numbers. Access to the data will be restricted to authorized members of the data management team. All data will be securely stored.

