#### Interim analyses

No formal interim analysis of treatment efficacy is planned, given the short treatment and follow-up duration of this trial. However, independent of any efficacy assessment, a pre-specified safety stopping rule has been established. The DMC will conduct an ad hoc safety review whenever any of the following occurs in either study arm: (1) the incidence of major bleeding (defined by ISTH criteria) reaches or exceeds 20% of enrolled participants in that arm; (2) two or more cases of heparin-induced thrombocytopenia (in the UFH arm) or two or more cases of severe anaphylactoid/hyperkalemic reactions attributable to nafamostat mesylate (in the NM arm) are reported; or (3) any single adverse event is judged by the treating physician and confirmed by the DMC to be directly and probably related to the study anticoagulant and life-threatening. Upon triggering any of these thresholds, the DMC will unblind and review the relevant safety data and may recommend continuation without modification, protocol amendment (e.g., dose adjustment or revised monitoring), or early termination of the trial to the trial steering committee. These numerical thresholds will be reviewed and, if necessary, refined by the DMC biostatistician prior to trial initiation.

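### The blinding claimed for data collectors and analysts is not delivered by the roles the article describes

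*Protocol article*

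**What the plan says.** The article makes several blinding claims, each covering different people.

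- Allocation concealment mechanism: "the randomized results will not be known to the personnel involved in data collection and statistics". This is the only place that includes data collectors.
- Who will be blinded, and Procedure for unblinding if needed: clinicians are open, while outcome assessors and statisticians are masked.
- Data management: the data management team does not know allocation.
- Strengths and limitations: assessors, adjudicators and the statistician are masked.

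The work is assigned as follows.

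- Plans for assessment and collection of outcomes: "the researchers will collect the necessary data based on the results of the laboratory tests, and record the therapeutic measures taken", together with disease progression and all adverse events. The researchers also score SOFA and APACHE II at enrolment. Both scores are among the follow-up data, and no separate masked scorer is named.
- Strategies to improve adherence to interventions: "The researchers will monitor the patients’ compliance through bedside checklists and daily review of treatment records".
- Data management, on the masked team: "They were responsible for regular data audits and source data verification. In addition, this independent data management team was also responsible for the statistical analysis". Before analysis, personal identifiers are replaced by a study number. No other masking step is described.

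On patients, Strategies to improve adherence states: "The patients are unaware of the intervention measures they are receiving". Procedure for unblinding if needed states: "No blinding was implemented for participants or clinicians".

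**The concern.** A blinding claim is only as good as the separation of duties behind it. Here the intervention is itself one of the treatments to be recorded, and the records of an open-label trial will show which anticoagulant ran. Staff who record treatments, or who check the case report form against the source, learn the arm unless something is hidden from them. The article describes nothing of that kind.

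The outcomes exposed are those that involve judgement by someone reading the chart: SOFA and APACHE II scoring, and the recording and classification of bleeding and other adverse events. On the analysis side, the article names adjustment covariates only by example and leaves multiple imputation to be used when needed, so an analyst who knows the arms could be influenced in making such choices. Mortality and laboratory values are little exposed. Readers of the eventual report would credit a safeguard that the described organisation does not provide.

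**Working it through.** No arithmetic decides this point. The only design figure is the sample size, which reproduces and is not affected. With a difference of 4 h, SD 8 h, two-sided alpha 0.05 and power 80%: n per arm = 2 × (1.960 + 0.842)² × (8/4)² = 2 × 7.85 × 4 = 62.8, rounded up to 63. With 10% dropout, 63 / 0.90 = 70 per arm, so 140 in total. Both match the article.

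The check sets claim against role.

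**Data collectors.** Claim: they do not know allocation (Allocation concealment mechanism). Role: they record the treatments given and adverse events (Plans for assessment and collection of outcomes). The trial is open-label (Who will be blinded). The drugs are prescribed in different units, mg/h for nafamostat and U/kg/h for heparin (Intervention description), and changes to the assigned drug are documented with reasons (Criteria for discontinuing or modifying allocated interventions). A person who records treatments under these conditions sees the arm. The claim and the role conflict directly.

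**Verifiers and analysts.** Claim: the data management team does not know allocation. Role: the same team verifies source data and runs the final analysis. Masking described: personal identifiers only, which does not hide drug, dose or arm. If verification includes the anticoagulant record, the team learns the arm for each record checked. The number exposed therefore depends on how much is verified, which the article does not state; the ceiling is all 140 planned participants. Verification also reaches events that point to one arm: the Interim analyses section ties heparin-induced thrombocytopenia to the heparin arm, and attributable anaphylactoid or hyperkalemic reactions to the nafamostat arm.

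**Participants.** One section says that patients do not know their treatment; another says that participants were not blinded. An unmasked patient might in practice not know the drug, but as descriptions of the design the two statements are incompatible.

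**The case against.** The strongest reply is that this is a condensed article. It speaks of a team, and of authorised members within it, so verification and analysis may be done by different people. Masked extracts, coded arms and task splits are commonly set out in a data management plan or SAP that is not shown. That stands as a reason not to say that the blind is impossible. It does not remove the point, because the article itself assigns both tasks to one team and still asserts that the team is masked.

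It is also fair that the choice between the t-test and the Mann–Whitney test follows a normality test rather than discretion, and that the Limitations text names objective circuit-stopping criteria, not blinding, as its main protection for the primary outcome. That text openly concedes residual bias. Both limit what is at stake.

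A reader might infer stronger things that the document does not support:

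- *That the same individuals open envelopes, give the drug and collect data.* The article uses generic role names throughout, so identity of persons is inference. The conflict does not need it.
- *That the safety triggers must go undetected or unblind the analysts.* This is tempting because the bleeding trigger is counted by arm ("reaches or exceeds 20% of enrolled participants in that arm") while Confidentiality says: "Access to the data will be restricted to authorized members of the data management team". But adverse events also go to the study coordinator and the ethics committee, and a monitoring committee that includes a statistician regularly reviews safety data. A route outside the analysis team exists.
- *That the circuit adjudicators are unblinded.* They are described as outside the research and masked, and nothing contradicts that.

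**Conclusion.** The point holds as a mismatch between stated blinding and described roles. For data collectors, the contradiction is in the text. For the analysts, it rests on one assumption: that source verification covers treatment records with the anticoagulant visible, and that the team is not split internally. The article describes neither redaction nor a split. The two statements on patient blinding contradict each other outright.

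The size of any bias cannot be derived from the document. The exposure is at most 140 participants' records and bears mainly on chart-based scores, adverse-event recording and analysis choices. Much of the bias risk for the primary outcome comes from unmasked bedside staff, which the article already acknowledges. This should be corrected, but it does not invalidate the design.

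**What to change.** 1. Assign source verification of anticoagulant, dose and other arm-revealing fields to existing staff who take no part in the analysis.
2. Give the analysts a dataset with arms coded A/B, and withhold drug and dose fields until the primary analysis choices and result are locked.
3. Correct Allocation concealment mechanism to say that data collectors are not blinded. Limit the claims in Who will be blinded, Procedure for unblinding if needed, Data management, and Strengths and limitations to the roles that are actually masked.
4. Reconcile Strategies to improve adherence with Procedure for unblinding on whether participants are blinded.

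If a split between verifiers and analysts already exists, one sentence in Data management saying so, and saying what is masked, would settle the analyst part.

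The cost is a reassignment of existing duties, a coded dataset and some rewording. The downside is small: the blinding claim reads less favourably, and some fields are merged later. Sample size, endpoints and treatment do not change.

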#### Confidentiality

The personal information of all participants will be replaced by unique identification numbers. Access to the data will be restricted to authorized members of the data management team. All data will be securely stored.

#### Plans for collection, laboratory evaluation and storage of biological specimens for genetic or molecular analysis in this trial/future use

Not applicable. This study will not involve the collection, storage, or analysis of biological samples.

### Statistical methods

#### Statistical methods for primary and secondary outcomes

Continuous variables were tested for normality using the Kolmogorov–Smirnov test. Normally distributed data were presented as mean ± standard deviation (SD) and compared using the independent-samples *t*-test. Non-normally distributed variables were reported as median (interquartile range, IQR) and analyzed using the Mann–Whitney U test. Categorical variables were expressed as counts (percentages) and compared using the χ^2^ test or Fisher’s exact test, as appropriate.

In addition, the primary endpoint of this study was the mean lifespan of the hemodialysis filter during CRRT. Kaplan–Meier survival analysis was conducted to compare the cumulative probability of filter life over time, with the log-rank test applied for group comparison. To control for potential confounders (e.g., disease severity scores), multivariable linear regression and Cox proportional hazards models were used as sensitivity analyses.

Secondary outcomes included the changes in disease severity scores (SOFA and APACHE II), pancreatic enzymes (amylase, lipase) and inflammatory biomarkers (PCT, CRP, IL-6, IL-10, TNF-α) measured on Day 1 (baseline), day 3, day 5, and day 7 after randomization. To evaluate time-dependent trends and group differences, a repeated-measures analysis of variance (RM-ANOVA) was applied for normally distributed variables. Baseline disease severity characteristics, including etiology, CTSI/EPIC radiological scores, and the presence and grade of intra-abdominal hypertension, will be summarized descriptively and compared between groups using the χ^2^ test, Fisher’s exact test, or the Mann–Whitney U test, as appropriate. The assumption of sphericity was tested by Mauchly’s test, and when violated, the Greenhouse–Geisser correction was used to adjust degrees of freedom. Differences in change-from-baseline values (ΔSOFA, ΔAPACHE II, and Δbiomarker levels) between groups were analyzed using the independent-samples *t*-test or Mann–Whitney U test, as appropriate. Correlations between the changes in inflammatory markers and changes in severity scores were assessed using Spearman’s rank correlation coefficient.

All participants who received at least one dose of study anticoagulant were included in the safety set. The incidence of adverse events (AEs), serious adverse events (SAEs), and bleeding or coagulation complications were summarized using descriptive statistics and compared between groups with the chi-square test or Fisher’s exact test, as appropriate.

All statistical analyses were performed using SPSS version 26.0 (IBM Corp., Armonk, NY, United States) and R version 4.3.0 (R Foundation for Statistical Computing, Vienna, Austria). A two-sided *p*-value < 0.05 was considered statistically significant.

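### The primary endpoint has two unranked group comparisons at 0.05, one of them chosen by a normality test; if either may count as success, the false-positive rate is about 6–10%, and the sized comparison of means may not be the one reported

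*Protocol article*

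**What the plan says.** The Sample size estimation section fixes one comparison. It uses "the approximate formula for comparing the means of two independent samples", with these inputs: "The assumed baseline value of approximately 30 h for the heparin group", "A minimum clinically important difference of 4 h", and a standard deviation of 8 h. The error rates are given as "Assuming a two-sided α level of 0.05 and a power (1–β) of 80" per cent. The result is 63 per arm, raised to 70 for 10% dropout.

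The section Statistical methods for primary and secondary outcomes does something different.

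- It opens with a rule for every continuous variable: "Continuous variables were tested for normality using the Kolmogorov–Smirnov test". Normal data go to a t-test with means; other data go to a Mann–Whitney test with medians.
- It then turns to the primary endpoint, mean filter lifespan, and adds a Kaplan–Meier analysis "with the log-rank test applied for group comparison".
- Multivariable linear regression and Cox models are labelled sensitivity analyses. The t-test, Mann–Whitney and log-rank tests carry no such label and are not ranked.
- The section closes with one threshold for all analyses: a two-sided p-value below "0.05 was considered statistically significant". No hierarchy or split of alpha is given.

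Under Outcomes, a circuit's life ends when staff take it out of service, including for treatment goal reached, death or the 72 h limit. Elective stops are classed as not due to clotting.

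**The concern.** Two problems follow, and they should be kept apart.

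First, there are two primary p-values and no rule saying which decides. They are correlated but not identical, so the chance that at least one falls below 0.05 under no treatment difference exceeds 5%. They can also disagree for a structural reason: a log-rank test can censor circuits stopped for reasons other than clotting, whereas a t-test or Mann–Whitney test takes the observed duration as it stands.

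Second, the normality step lets the data choose the estimand. If it rejects, the result is a rank comparison with medians, and neither estimates the 4 h mean difference that the protocol justifies in clinical and economic terms. If the log-rank result is read as decisive instead, its power was never calculated.

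At stake is the trial's single confirmatory claim: its error rate, its power and the quantity it reports.

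**Working it through.** **Reproducing the stated sample size.** Inputs from Sample size estimation: difference 4 h, SD 8 h, two-sided 0.05, power 80%.

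n per arm = 2 × (1.960 + 0.842)² × 8² / 4² = 2 × 7.85 × 4 = 62.8, so 63. With dropout, 63 / 0.90 = 70. Power at 63 per arm is 80.1% by the normal approximation and 79.5% by the noncentral t. The arithmetic is correct for a comparison of means.

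**False-positive rate.** Two independent tests at 0.05 would give 1 − 0.95² = 9.75%. The tests here are correlated, so the rate was simulated: no treatment difference, 63 independent observations per arm, 10,000 trials per row. The normality step was a Kolmogorov–Smirnov test in each arm with estimated mean and SD, and the rank test was used if either arm rejected. The documents give no distribution and no rate of non-clotting stops, so both are assumptions and were varied. All distributions have mean 30 h; extra stops are exponential with mean 60 h.

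| Assumed filter life | Censoring | t-test or Mann–Whitney | Log-rank | Either < 0.05 | Rank test chosen |
|---|---|---|---|---|---|
| Normal, SD 8 | 72 h only | 5.08% | 4.91% | 7.05% | 9.6% |
| Normal, SD 8 | plus extra stops | 4.99% | 5.00% | 9.15% | 36.8% |
| Log-normal, SD 8 | 72 h only | 5.24% | 5.24% | 7.22% | 53.7% |
| Log-normal, SD 8 | plus extra stops | 4.96% | 5.72% | 9.78% | 36.4% |
| Log-normal, SD 20 | 72 h only | 5.06% | 5.29% | 7.24% | 97.8% |
| Log-normal, SD 20 | plus extra stops | 4.52% | 5.50% | 8.60% | 92.7% |
| Exponential | 72 h only | 4.94% | 5.18% | 7.12% | 99.6% |
| Exponential | plus extra stops | 5.04% | 5.32% | 8.44% | 99.98% |

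A separate simulation with 63 per arm gave 6.4–7.5% with censoring only at 72 h and 7.7–9.9% with extra stops. Together the range is about 6–10%. Each comparison taken alone stays near 5%, so the excess comes from having two of them.

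**How often the sized test is replaced.** See the last column. The 9.6% for normal data is the nominal false rejection in either of two arms, 1 − 0.95² = 9.75%.

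**Power of the log-rank test.** 30 vs 34 h, SD 8 h, 63 per arm, 5,000 trials per setting:

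- Censoring only at 72 h: 72.3% (normal) and 63.2% (log-normal). The separate simulation gave about 71% and 65%. The normality-selected test had 79.1% and 81.0%.
- Extra stops added: 55.4% and 52.5%. The normality-selected test fell to 21.4% and 25.1%. In this setting the 4 h was placed on time to clotting, so the difference in observed service life is less than 4 h. These figures therefore do not contradict the sized 80%, which supposes 4 h in the analysed durations. They show how much depends on which quantity is named.

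**The case against.** The strongest reply is that the protocol states no rule allowing success on either test. The opening paragraph of the methods is generic, the next paragraph attaches the log-rank test to the primary endpoint, and ranking analyses is commonly left to an analysis plan that is not shown. This stands in part: the inflation is conditional on either p-value being read as success. It does not dispose of the point. The article itself writes both comparisons for this endpoint, gives the sensitivity label only to the regressions, and sizes a third thing. An analysis plan would have to correct that text, not merely add to it.

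Several stronger readings are tempting and are not supported.

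- *That the normality step inflates the error rate.* It does not: 4.5–5.2% in every setting.
- *That the 72 h limit makes filter life non-normal.* On the stated figures the limit is (72 − 34)/8 = 4.75 to (72 − 30)/8 = 5.25 SDs above the mean and almost never binds. Frequent replacement of the t-test needs skew or extra stops, which are assumptions, although the protocol concedes that reported SDs vary widely.
- *That 63 per arm is valid only for the t-test.* With the same inputs the Mann–Whitney test has about 77% power (normal) or 83% (log-normal). What is lost is the estimand, not much power.
- *That the error rate is far above 10%.* That requires several correlated filters per patient analysed as independent, which is a separate problem and would persist with one named test. The documents give neither the number of filters nor their correlation, and the sample size counts cases.
- *That log-rank power is a third or less.* That follows from a constant hazard, which implies an SD equal to the mean, about 30 h, against the stated 8 h.

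**Conclusion.** The point holds in a limited form. The primary endpoint has two unranked comparisons at two-sided 0.05. If either may count, the false-positive rate is about 6–10% instead of 5%; this rests on assumed distributions and censoring and on independent observations at 63 per arm. Every setting tried exceeded 5%, and none reached 10%.

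The normality step adds a different harm: the reported test and summary may not address the 4 h mean difference, in about 10% of trials if the data are normal and up to nearly all if they are strongly skewed. If the log-rank test were taken as decisive, the stated 80% power would not apply: about 63–72% with censoring only at 72 h, and about 52–55% under the assumed extra stops.

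A reader might infer that the protocol intends to claim success on whichever test is significant. It does not say so; it only fails to prevent it. The sample-size arithmetic itself is sound. The change should be made, because it is cheap and concerns the one confirmatory claim.

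**What to change.** Before any outcome data are seen:

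1. Exempt the primary endpoint from the Kolmogorov–Smirnov rule.
2. Name one decisive test and estimand. The simplest is the between-arm difference in mean filter life per patient, with a 95% confidence interval and a two-sided 0.05 test. It matches the stated endpoint and is already sized at 63 per arm (70 with dropout), provided that the 4 h and 8 h figures describe service life as defined under Outcomes, where life ends at any discontinuation.
3. If the log-rank test or another time-to-event measure is preferred, name that instead, say how non-clotting stops are treated, and restate the power. A clot-free measure would be a different endpoint from the one defined.
4. Label the remaining tests, together with the regressions, as supportive with no separate claim.

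The cost is a few sentences if the comparison of means is named, plus a new power calculation if it is not. The sponsor gives up the option to choose a test later, and the stated power may fall if a time-to-event test is chosen.
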